## Background

Clean intermittent self-catheterisation (CISC) is a frequently used intervention for people who cannot empty their bladder effectively due to bladder outlet obstruction or failure of bladder muscle contraction which may be associated with neurological disease [1]. Patients needing CISC are taught how to insert a catheter, drain the bladder and then remove the catheter [2]. Single-use disposable catheters, typically with a hydrophilic coating, are predominantly used in the UK [3].

There are no accurate prevalence data for CISC use in the UK. The National Health Service (NHS) England prescription database recorded 47 million CISC catheter prescriptions in 2010 at a cost of £64 million [4]. If we assume each individual uses an average of 25 catheters per week, this suggests that there are about 36,000 CISC users in England and perhaps 43,000 in the UK as a whole. This estimate is in agreement with a primary care-based estimate which found a prevalence of approximately 7–8 per 10,000 adults, suggesting an approximate total of 43,000–49,000 adults in the UK ([name], personal communication, August 2011).

Recurrent urinary tract infection (UTI) is the commonest adverse event experienced by CISC users affecting between 12–88 % of studied cohorts [5]. Differentiation between asymptomatic bacteriuria, which would not normally be treated, and symptomatic UTI in these studies is difficult. One estimate suggests that 50 % of users have persistent bacteriuria and at least 25 % suffer two or more symptomatic UTI episodes per year [6]. Conservatively this suggests that up to 10,000 CISC users in the UK suffer recurrent UTI, the target population for this trial. Neurological disease, female sex, young age and high bladder volumes are associated with higher prevalence of UTI [1]. *Escherichia coli* (*E. coli*) is the causative bacterium in 60–70 % of cases [6]. Most episodes are associated with transient symptoms such as lower abdominal pain, urethral pain and flu-like symptoms; occasionally systemic upset can occur with fever and loin pain. Those with reduced bladder sensation may alternatively complain of cloudy urine, increased odour and incontinence [7]. Recurrent UTI is distressing and an additional burden for patients with underlying neurological disease and functional disability [5]. For some there is a risk of renal damage in the longer term [7] or significant sepsis requiring intensive care and potential mortality.

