#### Secondary objectives

The secondary objectives are as follows:Clinical○ Determine the relative effect on quality of life (QoL) amongst trial participants○ Measure overall satisfaction with prophylactic antibiotic treatment○ Assess participants’ perception of benefit at 12 months using qualitative methodology○ Record adverse effects related to both prophylaxis and treatment antibiotic use○ Determine relative rates of hospitalisation because of UTI○ Measure difference in renal function by estimated glomerular filtration rate (eGFR) at 12 months○ Determine rates of asymptomatic bacteriuria at 12 months○ Assess ecological change in *E. coli* isolated from urine and perianal swabsEconomic○ Measure incremental cost per QALY gained through repeated completion of SF-36○ Assess participants’ willingness to pay to avoid a UTI by contingent valuation at end of trial participation and incorporate these data in the economic evaluation using a cost-benefit framework.

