### Secondary outcome measures

Secondary outcome measures will be collected as additional criteria to the primary outcome from inspection of participant healthcare records, by participant questionnaire or by clinical test performed at specific time points. The following are also included.The rate of UTI will also be alternatively defined as the *incident density rate*; the number of UTIs suffered during the observation period minus days spent taking treatment courses of antibiotics active against urinary tract organisms.*Febrile UTI* defined as the primary outcome plus presence of a recorded fever of more than 38 °C:○ Confirmed by inspection of primary or secondary healthcare record by research staff.*Microbiologically confirmed symptomatic UTI* defined as the primary outcome plus positive urine culture:^1^○ Participants will provide an intermittent catheter specimen of urine for local analysis as requested by the treating clinician. This will be analysed according to clinician decision by the local microbiology using the local standard operating procedure (SOP). We will also ask the participant to send a urine specimen using provided safe packaging to the central microbiology trial laboratory in the Newcastle upon Tyne Hospitals NHS Foundation Trust each time they consider they have symptoms suggestive of UTI and intend to commence a course of antibiotic treatment. This will be analysed and cultured on receipt and the result used for trial outcome purposes but not for patient care.*Antibiotic prescription for asymptomatic UTI* without participant-reported or clinician recorded evidence of symptom change.*Asymptomatic bacteriuria* defined as a positive urine culture in the absence of symptoms.○ Participants will be asked to send a urine sample to the central laboratory at baseline prior to randomisation and during asymptomatic periods in months 3, 6, 9 and 12 of their trial participation. They will also be separately consented to provide a urine sample 6 months after completion of trial (18-month time point).*Hospitalisation due to UTI* defined as an unplanned visit to hospital for treatment of a UTI which required at least one overnight stay in hospital.○ Collected from healthcare record review and checked from participant report or enquiry.*Participant perception of benefit.*○ We will record and analyse semi-structured interviews with up to 30 participants purposively sampled from both trial arms on completion of their 12-month trial period.*Overall satisfaction with allocated treatment strategy.*○ Participants will complete the treatment satisfaction questionnaire for medication at 12 months as part of their completion of trial questionnaire [20].*Generic health-related quality of life.*○ Participant completion of the SF-36 1-week recall questionnaire at baseline, 3, 6, 9 and 12 months and within the first 2 days of each episode of symptomatic antibiotic-treated UTI [21].

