#### Sources of bias

To allow randomisation, eligible participants and the responsible clinician will both need to be sufficiently uncertain of whether the experimental or control strategy is better for relief of recurrent UTI considering each individual’s particular circumstances. Given the lack of high-level evidence as to which is more effective, we will provide trial information illustrating the uncertainty and the need for a definitive trial. This will act to ensure that any selection bias in terms of characteristics of CISC users willing to be randomised is minimised. An anonymised screening log will be kept at each site listing demographic and clinical characteristics and reasons for declining randomisation (if offered) and used for comparison of this group with those entering and those completing the trial. Secondly the characteristics of participants who cross over at randomisation or at a later stage, withdraw or regret their allocated treatment option may differ from those completing 12 months of their allocated strategy. We will address this by comparison of SF-36 scores between these groups measured at baseline prior to randomisation and following treatment. Trial literature given to all participants and to their clinicians will detail other measures to reduce the risk of UTI such as adequate fluid intake, increased frequency of catheterisation, cranberry products and, if appropriate for post-menopausal women, vaginal oestrogen supplements.

Given the lack of blinding, it is possible that participants allocated to the control of no prophylaxis will be more likely to seek treatment for symptoms suggestive of UTI, and that their clinicians may be more likely to prescribe treatment antibiotic, thus introducing bias to our primary outcome. To reduce the potential for this bias, we will give information on the use of antibiotic treatment, describing indication and choice of agent, in trial literature to participants and their GPs according to established guidance from the British Infection Association (BIA) and other groups. We will also include in the participant information packs advice on when to seek help regarding symptoms suggestive of UTI and the use of simple measures to avoid or avert symptomatic UTI. To ensure uniformity of processing and culture techniques, we will use the results of analysis performed at our central laboratory for trial outcomes. The local result will be used for the study if the central result is missing.

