Urine and perianal swab specimens will be submitted regularly by participants during the trial to the central laboratory for selective culture of *E. coli*. These samples would not normally be collected during routine care, and the participants will be asymptomatic for UTI at the time of specimen collection. We therefore do not plan to inform the participant or the clinicians responsible for their care of the results. This policy would be sensitive to clinical concerns and exceptions readily made if, for example, the participant suffered an episode of severe sepsis and the results of the cultures would be helpful to clinical care. Similarly we will not routinely inform treating clinicians of the result of any positive culture from CSU sent to the central laboratory during an episode of symptomatic UTI. The reason for this is the delayed transit time and hence prolonged period before any result is available. This in most cases would make the result unhelpful to clinical care. Participants will be encouraged to also take a urine specimen to their treating clinician for local analysis.

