### Statistical analysis

An analysis of the primary outcome measure (incidence of UTI) for the full study will be performed both for the full data set and for the separate sub-groups defined by high and low baseline UTI rate (as specified during stratification for the randomisation process) using both the Poisson rate test and an incidence density ratio approach to allow for the different treatment durations; regression or generalised linear modelling approaches will be used to adjust for the effects of covariates. The model selection process will include the stratification factors (prior rate of UTI, presence of neurological disease and gender) and other baseline variables (person doing CISC [self or other], asymptomatic bacteriuria, age, type of catheter, use of antibiotic prophylaxis for UTI in the previous 12 months prior to randomisation and presence of bladder augmentation). The inclusion of interaction terms such as site will also be explored. The inclusion of baseline values as covariates will additionally enable the examination of possible interactions between effects observed and these values. Not all covariates mentioned above will be included in the final model, but all will be considered during the model selection process.

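### Asymptomatic bacteriuria is defined as any positive urine culture, but the only method stated for the scheduled urines is selective culture of E. coli

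*Protocol article*

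**What the plan says.** Under Secondary outcome measures, the protocol article gives asymptomatic bacteriuria as "defined as a positive urine culture in the absence of symptoms". No organism is named. The outcome comes from urine sent to the central laboratory at baseline and "during asymptomatic periods in months 3, 6, 9 and 12 of their trial participation", with a further specimen at 18 months from those who consent. It serves a listed secondary objective: "Determine rates of asymptomatic bacteriuria at 12 months". The Statistical analysis section has it analysed in the same manner as the primary outcome. That section also lists it among the baseline variables considered for the primary model: "person doing CISC [self or other], asymptomatic bacteriuria, age, type of catheter".

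The laboratory method appears under Twelve months after randomisation. Urine and perianal swab specimens "will be submitted regularly by participants during the trial to the central laboratory for selective culture of" *E. coli*, and "the participants will be asymptomatic for UTI at the time of specimen collection". Under Sources of bias, "we will use the results of analysis performed at our central laboratory for trial outcomes", with the local result used only where the central one is missing.

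Two other places mention the same urines in broader terms. The Baseline section sends them for central microbiological analysis, and the section on months three, six and nine for analysis and storage. Neither names a culture method.

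**The concern.** The specimens sent for selective *E. coli* culture are the ones that must supply an any-organism outcome. They are the regular, asymptomatic, central-laboratory urines, and Table 1 schedules no second asymptomatic urine. A selective *E. coli* method is not designed to recover other organisms, and the Background says that *E. coli* "is the causative bacterium in 60–70 % of cases" of UTI. If the stated method were the whole method, a specimen positive only for another species would count as negative.

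Three things would suffer: the reported bacteriuria rate in each arm, the precision of the comparison, and possibly the treatment ratio itself. The ratio is distorted if prophylaxis acts differently on *E. coli* and on other organisms.

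**Working it through.** The document gives no sample size, power or expected rate for this outcome, so there is no figure to reproduce. The check has two parts.

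**1. Side-by-side reading**

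- Definition (Secondary outcome measures): any positive culture, from scheduled asymptomatic urines at the central laboratory.
- Method (Twelve months after randomisation): selective culture of *E. coli*, for regular asymptomatic urines and swabs together.
- Broader wording (Baseline; months three, six and nine): analysis of an unspecified kind. It permits a general culture but does not state one.
- Local fallback (Sources of bias): of little help, because no local urine is scheduled in asymptomatic periods.
- Contrast: urines sent with symptoms are described under Secondary outcome measures as analysed and cultured on receipt, with no organism restriction.

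The definition and the one stated method do not match.

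**2. Size if only selective *E. coli* culture is done**

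Inputs:

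- *E. coli* share *s* = 0.60 to 0.70 (Background). This is the share in UTI, borrowed here for asymptomatic carriage.
- Control carriage 0.50 (Background). This is persistent bacteriuria in users of intermittent catheterisation generally.
- Ratio for bacteriuria under prophylaxis 0.61 (0.44–0.87) (Background, from the cited review). It is a relative incidence rate, used here as a risk ratio.
- 158 completers per arm (Sample size calculation).
- Each positive specimen is treated as carrying either *E. coli* or another organism.

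*Under-counting.* Share of positives missed = 1 − *s* = 0.40 to 0.30. Of all control participants, 0.50 × 0.60 = 0.30 to 0.50 × 0.70 = 0.35 are detected, and 0.20 to 0.15 are missed.

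*Ratio.* Any-organism RR = *s* × RR(E. coli) + (1 − *s*) × RR(other). An *E. coli*-only culture reports RR(E. coli).

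| Effect of prophylaxis | Any-organism RR, *s* = 0.60 | Any-organism RR, *s* = 0.70 | *E. coli*-only RR | Distortion |
|---|---|---|---|---|
| 0.61 on all organisms | 0.61 | 0.61 | 0.61 | none |
| 0.61 on *E. coli*, 1.00 on others | 0.60 × 0.61 + 0.40 = 0.766 | 0.70 × 0.61 + 0.30 = 0.727 | 0.61 | favours prophylaxis |
| 1.00 on *E. coli*, 0.61 on others | 0.60 + 0.40 × 0.61 = 0.844 | 0.70 + 0.30 × 0.61 = 0.883 | 1.00 | favours no prophylaxis |

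*Power with no differential effect.* Two-sided 5 % comparison of proportions at one time point, 158 per arm: power = Φ[(p₁ − p₂ − 1.96·SE₀)/SE₁], where SE₀ uses the pooled and SE₁ the separate proportions.

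- Any organism: p₁ = 0.50, p₂ = 0.50 × 0.61 = 0.305; difference 0.195, SE₀ = 0.0552, SE₁ = 0.0541; power 0.946.
- *E. coli* only, *s* = 0.70: p₁ = 0.35, p₂ = 0.2135; difference 0.1365, SE₀ = 0.0506, SE₁ = 0.0500; power 0.772.
- *E. coli* only, *s* = 0.60: p₁ = 0.30, p₂ = 0.183; difference 0.117, SE₀ = 0.0482, SE₁ = 0.0477; power 0.682.

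**The case against.** The strongest reply is that the sentence about selective culture is not a laboratory specification. Its paragraph explains why results are not returned to participants and clinicians, and it does not say that no other culture is done. The broader wording in the Baseline and the three-, six- and nine-month sections fits a general culture for bacteriuria alongside a selective one for the *E. coli* ecology outcome. A footnote marker is attached to positive urine culture at the entry for microbiologically confirmed UTI. Its text is not shown and may define positivity. Plating detail is also commonly left to a full protocol or laboratory manual.

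This stands in part: a wider culture may well be done. But the article is not silent on method. It states one, and that one does not fit the outcome. If a general culture is done, the sentence needs completing; if not, the outcome needs renaming.

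A reader might infer three stronger conclusions, and the document supports none of them.

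- *That the specimens cannot yield the outcome.* Even with *E. coli*-only culture, some 60–70 % of positives would be found under the assumption above. That is under-ascertainment.
- *That the error favours prophylaxis.* This requires *E. coli* to be suppressed more than other organisms, and no organism-specific effects are given. The Background reports carriage of resistant *E. coli* rising from 40 % to 80 % under one prophylactic regimen in another population, so persistence of *E. coli* is also conceivable. Replacement by other species is plausible, but it is one scenario among several.
- *That the ecology outcome is undermined.* Secondary objectives and Adverse effects (harms) confine that outcome to *E. coli*, for which selective culture is suitable.

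**Conclusion.** The point holds as an inconsistency between an outcome definition and the only method stated for its specimens, and it should be corrected. If the method is followed as written, about 30–40 % of positives are missed, and illustrative power falls from about 95 % to 68–77 %. The treatment ratio may be unbiased or shifted either way. It favours prophylaxis only if *E. coli* is suppressed more than other organisms.

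These sizes rest on borrowing the UTI organism share for asymptomatic carriage, on 50 % control carriage, on reading 0.61 as a risk ratio, and on one organism type per positive specimen. They illustrate scale and are not forecasts.

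The reach is limited. The primary outcome is defined by symptoms and antibiotic treatment and needs no culture. It is touched only through baseline bacteriuria, which is a candidate covariate that may not enter the final model. That covariate is measured before randomisation, so treatment cannot make its misclassification differ by arm.

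**What to change.** Reconcile Secondary outcome measures with the specimen paragraph under Twelve months after randomisation, in one of two ways.

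1. State that scheduled urines receive standard non-selective culture, judged by the same positivity threshold as symptomatic specimens, and that selective *E. coli* culture is kept for the ecology and resistance outcome. If this is already laboratory practice, the cost is one sentence. If not, it is one routine plate per urine already received: 372 × 5 = 1,860 scheduled specimens at most, plus up to 372 at 18 months. No new sample or visit is needed.
2. If only selective culture is available, rename the outcome and the baseline covariate 'asymptomatic *E. coli* bacteriuria' and draw no conclusion about bacteriuria in general. This costs only wording, though the lower power remains.

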#### Data handling and record keeping

Data will be recorded by site staff authorised by delegation log on electronic case report forms (eCRFs) in the clinical data management software package (MACRO™). Data transferred from site to the secure validated database by remote access will be secure and encrypted. Data will be handled, computerised and stored in accordance with the UK Data Protection Act 1998. Under the trial participant consent, identifiable data will be stored in a separate and limited access database to allow preparation and sending of follow-up documentation. The quality and retention of study data will be the responsibility of the Newcastle CTU. All study data will be retained in accordance with the latest directive on Good Clinical Practice (GCP) and local policy.

Clinical data will be entered into the database remotely at each site by the local investigator or another member of the site research team with delegated responsibility for this activity, together with data from questionnaires completed at face-to-face visits with participants. Questionnaires returned by post to the trial management office will be entered there. Trial management staff and database management staff will work closely with local site research teams to ensure that the data are as complete and accurate as possible. The Newcastle CTU will be responsible for checking and requesting missing data. Two reminders will be sent to participants for prompt return of the questionnaires. Extensive range and consistency checks will further enhance the quality of the data. Data collected during the course of the research will be kept strictly confidential and accessed only by members of the trial team. Patients will be allocated an individual specific trial number to allow anonymised versions of the secure database to be available to the trial team and subsequently more widely under open data access arrangements. The management system will be used to ensure trial correspondence is sent to each participant using their preferred mode of delivery. To comply with the fifth principle of the Data Protection Act 1998, personal data will not be kept for longer than is required for the purpose for which it has been acquired. The sponsor is responsible for ensuring that trial data are archived appropriately. Essential data will be retained for a period of at least 10 years following close of study in line with sponsor policy and the latest directive on GCP (2005/28/EC). Caldicott approval for use, transfer and storage of participant identifiable information will be obtained at each site.

#### Data sharing

Data will be archived in accordance with the Newcastle CTU standard operating procedure (SOP) and European Commission Directive 2005/28/EC Article 17 and made permanently available to the wider research community through deposition at the UK Data Archive. Research participants’ confidentiality will be protected through the removal of personal, confidential and sensitive data. In addition to data files (rendered as CSV-delimited text), data list files will provide descriptions of all variables, including how each variable was constructed and calculated where appropriate.

#### Discontinuation rules

The trial may be prematurely discontinued on the basis of new safety information or for other reasons given by the Data Monitoring Committee (DMC) and/or Trial Steering Committee (TSC), sponsor, regulatory authority or ethics committee concerned. The TSC will give advice on whether to continue or discontinue the study and make a recommendation to the funder and sponsor. If the study is prematurely discontinued, active participants will be informed and no further participant data will be collected.

